## Abstract

**Background:**

High-quality cancer information resources are available but underutilized by the public. Despite greater awareness of the National Cancer Institute's Cancer Information Service among low-income African Americans and Hispanics compared with Caucasians, actual Cancer Information Service usage is lower than expected, paralleling excess cancer-related morbidity and mortality for these subgroups. The proposed research examines how to connect the Cancer Information Service to low-income African-American and Hispanic women and their health care providers. The study will examine whether targeted physician mailing to women scheduled for colposcopy to follow up an abnormal Pap test can increase calls to the Cancer Information Service, enhance appropriate medical follow-up, and improve satisfaction with provider-patient communication.

**Methods/Design:**

The study will be conducted in two clinics in ethnically diverse low-income communities in Chicago. During the formative phase, patients and providers will provide input regarding materials planned for use in the experimental phase of the study. The experimental phase will use a two-group prospective randomized controlled trial design. African American and Hispanic women with an abnormal Pap test will be randomized to Usual Care (routine colposcopy reminder letter) or Intervention (reminder plus provider recommendation to call the Cancer Information Service and sample questions to ask). Primary outcomes will be: 1) calls to the Cancer Information Service; 2) timely medical follow-up, operationalized by whether the patient keeps her colposcopy appointment within six months of the abnormal Pap; and 3) patient satisfaction with provider-patient communication at follow-up.

**Discussion:**

The study examines the effectiveness of a feasible, sustainable, and culturally sensitive strategy to increase awareness and use of the Cancer Information Service among an underserved population. The goal of linking a public service (the Cancer Information Service) with real-life settings of practice (the clinics), and considering input from patients, providers, and Cancer Information Service staff, is to ensure that the intervention, if proven effective, can be incorporated into existing care systems and sustained. The approach to study design and planning is aimed at bridging the gap between research and practice/service.

**Trial Registration:**

NCT00873288

## Background

The burden of cancer falls most heavily on poor ethnic minorities - particularly African Americans and Hispanics [1]. Overcoming such disparities requires finding effective ways to increase the use and impact of scientifically accurate cancer information. Excellent, free resources, such as the National Cancer Institute's Cancer Information Service (CIS) exist and have potential to transmit needed information to underserved groups. However, despite greater awareness of the CIS by low-income African American and Hispanic adults, actual CIS usage is lower than expected, paralleling excess cancer-related morbidity and mortality for these subgroups [2]. The planned study will examine the efficacy of a targeted physician mailing designed to connect the CIS to low-income African American and Hispanic women who need cancer-related information due to a scheduled colposcopy to follow up an abnormal Pap test.

### Cancer Information Service

Established in 1975, the CIS is a health communication service designed to help meet the cancer information needs of the general public, health professionals, cancer patients, and their family members and friends [3]. Most users access the CIS via a [contact]-CANCER) and are connected to English- or Spanish-speaking information specialists. Information specialists are highly trained in both informational and the interpersonal aspects of cancer communication and are adept at addressing a wide range of cancer inquiries, including cancer prevention and control [2]. The CIS Partnership Program, dedicated to addressing cancer health disparities, works with partner organizations that have an established, trusted presence in the community. The CIS Research Program seeks to advance cancer related health communication science by designing, implementing, and disseminating results of innovative studies in a manner that bridges the gap between cancer research and service [4].

Awareness data from the 2003 National Health Information National Trends Survey suggest that the CIS is reaching the underserved. Awareness of the CIS was greater among minorities (51% of Hispanics, 45% of African Americans) than Whites (28%), contrasting with the opposite demographic awareness pattern for NCI, NIH, and ACS. Also, CIS awareness increased as income and education decreased and was greater among those without health insurance than those with it [2]. However, awareness data contrasted markedly with actual usage data showing that more Whites (83%) than African Americans (13.4%) or Hispanics (2%) called the service. These findings suggest barriers to use of the CIS by underserved minorities, despite good awareness.

The planned research stems from three premises. First, a strategic partnership between health care providers and the CIS can overcome call barriers and be advantageous to patients and providers [2,5]. Second, the CIS is ideally positioned to reach and meet the cancer information needs of the underserved, many of whom have telephone but no internet access. Third, the CIS can play an important role in overcoming communication barriers that contribute to cancer health disparities. Because the CIS enables continuous access to valid cancer-relevant information in the context of human interaction, implementing a strategic partnership between patients, CIS, and providers is consistent with the Institute of Medicine's call for care based on continuous healing relationships [6]. CIS offers a bridge between the underserved patients' preferred interpersonal source (the provider) and information that is available from family and friends in a low literacy community [7,8]. As such, CIS has the potential to positively impact multiple levels in an ecological model of public health communication [9,10].

### Effective public health communication

From an ecological perspective [9,10], disparities are grounded in a system of reciprocal influences at the intrapersonal, group, community, institutional, and population levels that impede optimal awareness, understanding, decision-making, and action about health. Effective public health communication interventions activate multiple channels to impact the different levels in the ecological framework [11]. Moreover, effective health communication initiatives make their outreach relevant to the intended audience [12]. The need to adopt an audience-centered perspective is especially strong when trying to connect with racial and ethnic minorities. Intrapersonal issues to be considered when making outreach to low-income African Americans and Hispanics include language and attitudinal barriers, low health literacy, lack of information, and misinformation about cancer screening, risk, and treatment [13-16].

Two widely used modes of audience-centric outreach are targeting and tailoring. ***Targeting***, which utilizes a market segmentation approach, creates messages to reach a specific population segment or group, often defined by shared demographics like ethnicity or language. Targeting of physician mailing in the proposed research will be performed on the basis of medical condition, clinic/ethnicity, and language. Of necessity, targeting addresses only surface, observable characteristics [17]. ***Tailoring***, in contrast, creates messages to reach a specific individual whose characteristics are determined by assessment. Because a skilled, non-time-constrained human can tailor messages much more effectively than a computer [18], CIS information specialists highly trained in interpersonal communication will be the tailoring agents for this study.

At an interpersonal level, the underserved express a strong cultural preference for receiving health information verbally [14,19] and primarily from health care providers [20-22]. In the current health care environment, those preferences increase informational dependence on overburdened providers who are accurately perceived by patients as lacking time for discussion [23]. Augmenting the communication challenges, providers spend less time with the underserved [24], at least partly because low literacy patients ask few questions of medical professionals even when language barriers are not an issue [19,25,26]. There is a tendency for both underserved patients and their providers to emerge from the medical encounter dissatisfied, and with patients feeling that their information needs have not been adequately addressed [27,28]. By virtue of the CIS's availability to the public, and the diverse and well-trained staff [29], information specialists potentially offer a vital resource to bridge this gap between underserved patients and their health care providers.

### Sustainability

Innovations at the institutional level occur most often when a recognized need and the means to resolve it emerge in tandem [30]. Such systems can be described as balancing "need-pull" with "technology-push". The time constraints of providers and unmet informational needs of low literacy patients represent a strong need that can be served by available CIS technology. A simple "push" in the planned intervention is the provider letter that alerts the patient to a medical risk and an information need. Explaining that the CIS call is to be discussed at the upcoming medical appointment frames the CIS in a culturally acceptable normative context as a provider-extender rather than an outsider. Patients who are activated to discuss CIS calls at the medical visit give a reciprocal "push" that helps educate providers. By suggesting questions to ask of the CIS, the intervention prompts patients to learn about information gathering behavior, creating communication skills that may generalize to the medical encounter. The intervention is sustainable as a part of institutionalized office practice [31,32].

To maximize public health impact, the CIS needs to reach large new populations of underserved individuals whose cancer information needs are presently unmet [33]. The population at risk for cancer represents a good target because it is larger than the population of those already diagnosed with cancer. Thus, the planned intervention has potential to be sustained and increase CIS impact among the underserved.

### Cervical Cancer Disparities

African American women have both increased incidence and the highest rate of mortality from cervical cancer, showing mortality rates more than twice that of non-Hispanic Whites [34]. Survival is also lower among Hispanics, largely because of more advanced cancer at the time of diagnosis [1]. As many as 50% of medically underserved women in the National Breast and Cervical Cancer Early Detection Program failed to receive appropriate follow-up for an abnormal Pap smear, with the likelihood of no follow-up being greatest for African American women [35]. Another recent study of the urban poor found an inadequate follow-up rate of 38%, despite opportunities for follow-up since 86% of women continued to receive care in the same place [36].

Misinformation, lack of information, fear, and embarrassment are all barriers to receiving adequate follow-up care. Predictors of good follow-up are remembering receiving a letter from the provider, knowing the Pap result, being able to report the result correctly, understanding the purpose of colposcopy, having low fear of pain, and feeling confident that the provider will understand the patient's needs [37,38]. Consistent with the health belief model [39], therefore, accurately perceiving one's susceptibility to cervical cancer, feeling confident about being able to take protective action, and perceiving prognostic benefits (versus fatalism) of follow-up for early detection are associated with better follow-up. Telephone outreach addressing these domains has been demonstrated to be effective in increasing follow-up adherence to colposcopy by low-income, inner-city women [40]. An innovation in the proposed research is that telephone support will be provided by CIS information specialists.

### Study Aims

Using formative and experimental research methodologies, the planned research will investigate how to connect the CIS to low-income urban African-American and Hispanic women with abnormal PAP tests. Specific aims are to examine whether a targeted physician mailing can increase calls to the CIS, enhance appropriate medical follow-up, and improve satisfaction with provider-patient communication at the follow-up medical visit.

## Methods/Design

### Study sites and phases

Study procedures were reviewed and approved by Northwestern University's Office for the Protection of Research Subjects Institutional Review Board. The research will be conducted in two large community clinics that serve poor, ethnically diverse communities in Chicago. At the Erie Family Health Center (EFHC) on Chicago's West side, 82% of clients live at or below the federal poverty level; 57% have no health insurance; 90% are Hispanic or Latino. At Prentice Ambulatory Clinic (PAC) on Northwestern's Chicago campus, outpatient services are provided to a population that is 90% Medicaid/Medicare and 85% minority (60% African American, 30% Hispanic).

The initial, formative phase of the research will solicit input from patients and providers regarding all materials planned for use in the experimental phase of the study (e.g. questionnaires, consent procedures, and intervention materials). The experimental phase will follow comparing the intervention and control conditions.

### Formative phase

The formative research phase will acquaint the project team with the clinics. Next, focus groups with patient and providers will be conducted in each of these clinics.

#### Participants

Participants for the formative phase will be selected to be representative of the population at each clinic. Inclusion criteria for patients will be women over the age of 18 years who have had a pap test in these two clinics and who agree to participate. Inclusion criteria for providers will be any provider who administers pap tests and conducts colposcopy testing for women at the two clinics and are available to participate. Patients and providers will be consented prior to conducting the focus groups.

#### Focus groups

The project staff will conduct 4 focus groups of 5 participants each: 5 patients from EFHC, 5 providers from EFHC, 5 patients from PAC, and 5 providers from PAC. The patient focus group at EFHC will be co-facilitated by staff that is fluent in Spanish. Topics to be discussed in the focus groups are: a) perceived information support needs and barriers to following up abnormal Pap tests (e.g., fears, embarrassment, misinformation, kinds of information and messages desired, kinds of messages deemed unhelpful), b) feedback on the letters and assessment instruments planned for the randomized controlled trial (RCT) (e.g., reactions to calling the CIS service, reactions to inclusion of the word 'cancer' in the name of a service offering preventive care), c) familiarity with and views about the CIS, d) barriers and facilitators to telephoning the CIS for information about cancer prevention and screening. Focus groups will be audio taped to ensure the discussions are completely and accurately recorded.

#### Analysis

Focus group data will be transcribed verbatim by project staff. Staff fluent in Spanish will translate the Spanish focus groups in English and then transcribe them. Transcribed data from focus groups will be analyzed and interpreted via thematic analysis [41]. Three raters will read the transcribed materials thoroughly to identify themes for each topic. Codes for these themes will be developed and the responses will be tabulated using the coding scheme. Lessons learned will be discussed and will help guide tailoring the letter and assessment instrument for the RCT.

### Experimental phase

#### Study Design

The experimental phase of the study will be conducted using a two-group prospective RCT design comparing the effects of two provider mailing conditions: control (Usual Care) versus intervention (CIS + Questions). The RCT design will be 2 × 2 factorial with Clinic (EFHC versus PAC) and Letter (Usual Care versus Intervention) as between subjects factors.

#### Participants

This study aims to recruit 500 women with an abnormal annual Pap test and follow-up scheduling for colposcopy at EFHC or PAC. Based on the current patient flow in the two clinics, we expect to randomize approximately 100 women from EFHC and 400 from PAC. Entry criteria will include women of age 18 or older who speak either English or Spanish and who have received an annual Pap test that warrants scheduling for colposcopy at EFHC or PAC. Women scheduled for a repeated Pap test or repeated colposcopy as follow up to a previous abnormality will not be enrolled because they may already have completed their initial information seeking process.

#### Randomization

Patients will be randomized to two conditions that involve different letters from the provider. *Usual Care *participants will receive a generic letter reminding them of their follow-up appointment. *Intervention *participants will receive a targeted letter reminding them of the follow-up appointment, asking them or someone they designate to call CIS, and suggesting some questions to ask.

The patient will be the unit of randomization and the project statistician will prepare and manage the randomization scheme. Separate randomizations will be performed for EFHC and for PAC. Usual Care and Intervention letters will be placed in envelopes. At the time randomization envelopes are selected, group allocation will be concealed from study staff and clinic staff so that there is no selection bias in the randomization process.

#### Intervention

As soon as the patient has received notification of the lab Pap test result and has been scheduled for a colposcopy appointment, the appropriate control or intervention letter from the provider will be sent, along with a letter informing the patient about the study. The Usual Care letter from the provider will confirm the abnormal Pap and remind the patient of the scheduled follow-up appointment for colposcopy. The Intervention (CIS + Questions) letter from the provider will convey the same appointment information as the Usual Care letter. It will, in addition, ask the patient or a designate to [contact]-CANCER and it will suggest some questions to ask about abnormal Pap tests and colposcopy. The suggested questions are: "What does an abnormal Pap test mean?", "What is colposcopy and what can I expect during colposcopy?", and "How will it benefit me to take the test?"

Consistent with the Institute of Medicine's [42] recommendation, the letters will be appropriate for reading skills at or below an eighth-grade level. The Lexile, a measure of reading difficulty, will be used to gauge reading level [43,44].

Letters will be written in the patient's primary language, Spanish or English. They will be mailed on PAC or EFHC letterhead with a signature per the patient's provider. Text will be typed double-spaced in large font, filling less than a page. Like all materials planned for use in the RCT, the proposed letters will be reviewed with community members and providers during the initial formative phase of the study. The final content of the Usual Care and Intervention letters will be based on input from patients and providers.

#### Outcomes and measures

##### Primary outcomes

There are three primary study outcomes 1) telephone calls to CIS (call volume); 2) timely completion of medical follow-up (within 6 months); 3) patient satisfaction with doctor-patient communication at medical follow-up.

##### Telephone calls to the CIS

The CIS will tabulate calls originating from the study. When CIS information specialists answer the telephone, they log call and caller information into a standard Electronic Call Record Form (ECRF). With the caller's consent, three customer service questions are asked of all callers:

1. Have you used our service before?

2. How did you find our number to call?

3. What is your home ZIP code?

The ECRF response field for Question #2, "How Found Out" (HFO) has many codes, e.g., 300 - TV, 400 - radio, 801- ACS etc., including blank codes that can be assigned to a specific promotion or research study. Four How Found Out response codes will be allocated to identify the conditions in this study: Code 1: PAC, Usual Care; Code 2: PAC, Intervention; Code 3: EFHC, Usual Care; Code 4: EFHC, Intervention.

Information specialists will follow a series of steps (see: ECRF programming below) to determine which, if any, of the four codes should be assigned to a call.

Operationalizing call tracking in this way produces de-identified data. Consequently, it will not be possible to link ECRF-coded call data to the patient's other individual level outcome data. To accomplish such linking, self-reported data on calls to CIS also will be collected from identified participants during the exit interview. This will allow exploratory examination of whether calling the CIS appears to mediate more timely follow-up and improved provider-patient interaction.

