##### Timely medical follow-up

Scheduling of colposcopy appointments will be tracked electronically and by exit interview. Timely medical follow-up will be operationalized by whether the patient keeps an appointment for colposcopy within six months of the initial abnormal Pap. Colposcopy is the primary disposition for abnormal Pap tests at EFHS and PAC. Clinic staff endeavor to schedule all patients within three months of the abnormal Pap. Colposcopy is performed on-site at both EFHS and PAC, in order to maximize continuity and follow-up. The procedure may be performed by the patient's primary care physician or by one of several doctors at each clinic who specialize in colposcopy.

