##### Patient satisfaction with provider-patient communication

Satisfaction with provider-patient communication will be assessed by the *Doctors Who Communicate Well *scale from the 2.0 Adult Core Survey of the Agency for Healthcare Research and Quality's *Consumer Assessment of Health Plans Study (CAHPS*^®^) [45-47]. The CAHPS scale consists of four items asking the degree to which the provider: listens carefully, explains things understandably, shows respect, and spends enough time with the patient. Each item has 5 response options: never, sometimes, usually, always, I didn't see the provider. The scale's developers recommend collapsing responses to a 3-category distribution by combining "never" and "sometimes" into a single category [48] yielding a 1-3 range per item, where higher numbers indicate better care. Validated in both English and Spanish [45-47], the *Doctors Who Communicate Well *scale shows excellent internal consistency (Chronbach's alpha = .86) and predicts the rated quality of health care [45]. Patients will complete the CAHPS immediately after the follow-up visit for colposcopy.

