##### Ancillary outcomes

To support exploratory analyses, patients and providers will be asked several additional questions at the medical follow-up visit.

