##### Patient exit interview

After completing the CAHPS, patients will be asked: 1) whether they telephoned the CIS, and if so, how many times; 2) whether any others telephoned the CIS on their behalf, and, if so whom; 3) their satisfaction with the CIS call experience; 4) other ways in which they sought information about screening; 5) whether the doctor who performed the colposcopy was their regular physician; 6) whether family members accompanied them to the visit.

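### Self-reported CIS calls are collected only from women who attend colposcopy, so they cannot show whether calling mediates timely follow-up

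*Protocol article*

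**What the plan says.** Under *Telephone calls to the CIS*, the protocol article explains that calls logged on the Electronic Call Record Form (ECRF) are de-identified, so that "it will not be possible to link ECRF-coded call data to the patient's other individual level outcome data". To supply the missing link, "self-reported data on calls to CIS also will be collected from identified participants during the exit interview". It then draws the inference at issue: "This will allow exploratory examination of whether calling the CIS appears to mediate more timely follow-up and improved provider-patient interaction".

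Four other places fix when, and from whom, that self-report is obtained:

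- *Patient satisfaction with provider-patient communication*: "Patients will complete the CAHPS immediately after the follow-up visit for colposcopy".
- *Ancillary outcomes*: the further questions to women and their providers are put at that same visit.
- *Patient exit interview*: "After completing the CAHPS, patients will be asked: 1) whether they telephoned the CIS, and if so, how many times".
- *Protocol sequence*: consent is taken in person when the woman arrives for colposcopy, and only those who consent there receive the exit interview.

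*Timely medical follow-up* defines the outcome as "whether the patient keeps an appointment for colposcopy within six months of the initial abnormal Pap". *Statistical analysis*, Aim 4, treats it as a yes/no variable.

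**The concern.** A mediation analysis of timely follow-up has to compare callers and non-callers on whether they attended, so it needs call status in women who did not attend as well as in those who did. The article provides call status for attenders only. The mediator is observed through the outcome, and nothing in the article describes asking non-attenders whether they called.

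This is more than a detail left to a fuller analysis plan. The article asserts that the data will support the analysis, and elsewhere describes a data collection that does not. If the analysis were run as described, an association between calling and timeliness would come from a sample already filtered on attendance. It could be reported as evidence that calling the CIS brought women to colposcopy, which is the mechanism the intervention rests on.

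**Working it through.** **Inputs** (*Statistical analysis*, Aims 3 and 4): 225 women per group for the follow-up analysis; anticipated follow-up 55% control and 75% intervention; stated exit-visit sample 293 (124 and 169); anticipated intervention call rate 40%.

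**1. Reproduce the stated sample.** Number with exit-visit data = group size × follow-up rate.
- Control: 225 × 0.55 = 123.75, rounded to 124.
- Intervention: 225 × 0.75 = 168.75, rounded to 169.
- Total: 292.5, or 293 from the rounded figures, as stated.

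So the plan itself equates the women with exit-visit data with those who complete follow-up.

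**2. Count those with no mediator value on the same base.**
- Control: 225 − 123.75 = 101.25.
- Intervention: 225 − 168.75 = 56.25.
- Total: 157.5 of 450 = 35%.

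On 250 per group the count would be 112.5 + 62.5 = 175 of 500, also 35%. The base of 450 is used here because it is the one that yields 293.

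**3. Outcome variation among women with a mediator value.** On these planning figures, timely follow-up in the interviewed sample is 100% v 100%, a difference of 0 in place of the anticipated 20 points.

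**4. Allow for late attenders.** A woman who attends and is interviewed after six months has outcome no and a call status. The article gives no rate for this, so let *f* be the assumed share of non-timely women who attend late and are interviewed. Timely share among interviewed = timely ÷ (timely + *f* × non-timely).

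| *f* | Control | Intervention | Difference | Still without call status |
|---|---|---|---|---|
| 0 | 100% | 100% | 0 | 157.5 |
| 10% | 123.75/133.875 = 92% | 168.75/174.375 = 97% | 4 points | 141.75 |
| 25% | 123.75/149.0625 = 83% | 168.75/182.8125 = 92% | 9 points | 118.125 |
| 50% | 123.75/174.375 = 71% | 168.75/196.875 = 86% | 15 points | 78.75 |

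The last column is 157.5 × (1 − *f*). Variation grows with *f*, but the never-attenders stay unobserved in every row.

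**5. What the gap does to the estimate.** Take the intervention arm with *f* = 0 and assume that 40% of its attenders report a call: 168.75 × 0.40 = 67.5 callers and 101.25 non-callers. Let *u* be the unobserved share of callers among the 56.25 non-attenders.
- *u* = 0: follow-up is 67.5/67.5 = 100% in callers and 101.25/157.5 = 64% in non-callers.
- *u* = 0.40: 67.5/90 = 75% and 101.25/135 = 75%.
- *u* = 1: 67.5/123.75 = 55% and 101.25/101.25 = 100%.

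Identical exit-interview data are compatible with a positive association, none, or a negative one.

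**The case against.** Several points on the other side are fair.

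**Late attenders.** A reader might infer that the outcome is constant among interviewed women and that nothing at all can be computed. The article does not support that. It sets no six-month limit on consent or interview, and its remark that clinics try to schedule within three months concerns scheduling, not attendance. Some interviewed women may have outcome no. This stands, but it rescues only a comparison of late with timely attenders, and those who never came remain missing.

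**Time to colposcopy.** The mediation sentence uses a comparative, and appointments are tracked electronically, so time from Pap to colposcopy could be related to self-reported calling. That could be described, but it is not the yes/no outcome the article defines. It also conditions on attendance and so cannot show that calling led women to attend.

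**Exploratory status.** The sentence is labelled exploratory, and no mediation model or power calculation is given. This limits the consequence. It does not make call status observable in women who were never asked.

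**Filling the gap from ECRF totals.** One might subtract self-reported callers from the recorded calls in each arm. The records count calls rather than women, a designate may have made the call, and arm is assigned from the caller's answer to a probing question. The Discussion itself says that neither source can verify the other.

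**Wider damage.** A reader might also infer that the randomised comparison of follow-up, or the whole mediation sentence, fails. Neither follows. Follow-up is compared by randomised group without using call status, and provider-patient interaction is measured at the same visit as the self-report, so that half remains feasible among attenders.

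**Conclusion.** The statement about timely follow-up is wrong as written: the data collection described does not permit it. Mediation of attendance is not identifiable from self-report gathered only from attenders. On the plan's own rates, 35% of women (157.5 of 450; 101.25 control and 56.25 intervention) have no mediator value, and the 293 who do are exactly the timely completers. That count rests on the anticipated 55% and 75% and on the plan's own treatment of the exit-visit sample. If some non-timely women attended late, the number without a call status would fall, but it would still include every never-attender.

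The point is confined to half of one exploratory sentence. It is worth correcting because the correction is cheap and the misreading it prevents concerns the trial's central mechanism.

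**What to change.** - In *Telephone calls to the CIS*, remove timely follow-up from the mediation statement.
- Keep the exploratory analysis of provider-patient interaction (satisfaction), labelled as conditional on attendance at colposcopy and consent there.
- For calls and follow-up, report ECRF call counts by clinic and caller-reported letter group beside follow-up rates by randomised arm and clinic. Present them descriptively, with no mediation claim, and do not call the ECRF counts call rates per randomised woman.

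The cost is a change of wording and the loss of one exploratory claim; sample size, primary outcomes and randomised comparisons stay as they are. If the sponsor wishes to keep the question, call status would have to be sought from all randomised women whether or not they attend, under suitable consent. That is a change to data collection, not to wording.
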